### Objectives

We have the following objectives in this trial:To establish recruitment pathways and trial teams in two trial sitesTo inform the recruitment and timeline of a future fully powered trial by establishing the number of participants initially identified, approached, consented, randomised and completedTo refine future trial procedures by establishing the acceptability and experience of the trial process to participants, including randomisation and completion of outcome measuresTo further assess the acceptability of the treatment via qualitative interviews and, based on input from trial participants and clinicians, to further refine and develop the treatment manual and the procedures for training, supervising and assessing the competence of trial therapistsTo determine the optimal primary outcome measure in a future trial by assessing the performance of selected candidate primary outcome measures with respect to level of acceptability to participants (completion rates, perceived burden) and participant-perceived relevance and valueTo inform estimation of sample size for a future trial by measuring data completeness at follow-up (participant attrition), SD of the likely primary outcome measure, and the variability of the comparator condition, treatment as usual (TAU), across individuals and sitesTo pilot a measure of resource use and to assess the feasibility and acceptability of candidate health economics measures to inform the future definitive trialTo identify, measure and cost the resources needed to deliver the intervention

We will also evaluate whether the following continuation criteria have been met prior to planning a future definitive trial:Trial participation does not lead to serious negative consequences (unexpected serious adverse reaction) for our participants.Any serious concerns about the acceptability and feasibility of the trial procedures can be rectified prior to a full trial.Follow-up data at 9 months are available for at least 60% of participants.At least 60% of patients in the intervention group complete treatment (attend at least 50% of possible sessions).

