#### Secondary outcome measures

Participants will complete the following measures at baseline and all follow-up points, representing candidate primary outcome measures for a future definitive trial: the Patient Health Questionnaire 9-item scale [27], which measures depressive symptoms; the ALS [28]; the Bipolar Disorder Recovery Questionnaire [29]; and the Quality of Life in Bipolar Disorder scale [30]. Participants will also complete the Generalised Anxiety Disorder 7-item scale [31]. At baseline, 9 and 15 months, the Bech Mania Rating Scale [32], the Hamilton Depression Rating Scale [33] (both observer-rated), and the Brief Adherence Rating Scale for medication adherence [34] will be completed, as will relevant sections of the Structured Clinical Interview for DSM-V [35] to assess both eligibility criteria, and presence of affective episodes during the follow-up period.

In addition, participants will complete the EuroQoL 5-dimension 5-level (EQ-5D-5L) instrument [36] and the 36-item Short Form Health Survey [37] in order to assess how feasible it is to use these measures in this population. This will allow us to identify potential reasons for incomplete data. In the future randomised controlled trial, the scores will be used to obtain utility values for deriving quality-adjusted life-years in order to estimate incremental cost-effectiveness ratio. Participants will be asked also to complete a resource use questionnaire (last 6 months or since last assessment point) to assess the feasibility of collecting health and social service use. Information on the resource use and costs of delivering the ThrIVe-B programme will be collected.

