### Data analysis

#### Quantitative data analysis

Patients’ demographic characteristics at baseline will be reported by treatment group. The primary analyses will be performed after 9-month follow-up and after data cleaning is completed and the database finalised. Further analyses will be performed after the final 15-month follow-up. No interim analyses are planned.

All analyses will be done on an intention-to-treat basis; included outcomes will be reported according to randomised allocation and regardless of the treatment actually received. There will be no possibility of participants allocated to the control arm receiving the intervention; it is possible that participants allocated to the intervention will in actuality receive none of the intervention or will not complete the intervention (defined as attendance of at least 50% of group sessions). All outcomes will be reported descriptively. At 9-month follow-up only, an inferential analysis will be performed for continuous outcomes only, reporting the relevant 95% CI for the between-group mean difference (intervention minus TAU), but no *p* value. Inferential analyses will include the randomisation covariates: site and baseline medication status. No interactions between intervention status and covariates are planned.

Proportions of participants recruited (of those approached) and those lost to follow-up at 3, 6, 9 and 15 months, will be reported with 95% CIs. All analyses will use complete case data only. No attempts to address missing data, such as multiple imputation, will be made.

The economic analysis will take the NHS and social care perspective. No covariate analysis or subanalysis will be conducted, because this is a feasibility trial and is not powered for such inferential analyses. Descriptive data for each arm will be reported with CIs for between-group comparisons. No *p* values will be reported.

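### The complete-case rule discards the baseline, 3- and 6-month scores of people lost by 9 months, so drop-out that differs by arm can bias the reported difference

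*Protocol article*

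**What the plan says.** In the Protocol article, Quantitative data analysis, the rule is categorical: "All analyses will use complete case data only. No attempts to address missing data, such as multiple imputation, will be made". The same section says "All analyses will be done on an intention-to-treat basis" and explains this as reporting by allocated arm whatever treatment was received. For continuous outcomes it plans a between-group mean difference at 9 months only, with a 95% CI and no p value. The covariates listed are site and baseline medication status. Neither the baseline score nor any earlier follow-up score is listed.

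Under Secondary outcome measures, the four candidate outcomes are collected repeatedly: "Participants will complete the following measures at baseline and all follow-up points, representing candidate primary outcome measures for a future definitive trial". The follow-up points are 3, 6, 9 and 15 months. The observer-rated scales are sparser: "At baseline, 9 and 15 months, the Bech Mania Rating Scale", together with the Hamilton scale, so they have no 3- or 6-month value.

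The retention criterion under Objectives is pooled over arms: "Follow-up data at 9 months are available for at least 60% of participants". The Sample size section plans 48 participants, 24 per arm, and expects 17% attrition at 9 months.

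**The concern.** A participant who returns baseline, 3- and 6-month scores but misses month 9 contributes nothing to the 9-month difference. The complete-case difference compares those who stayed. It is sound if staying is unrelated to the score, or related in the same way and at the same rate in both arms. Otherwise the two groups of completers are selected differently.

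A difference between arms is foreseeable here. One arm attends a 15-session group programme and the other receives usual care, and participants know their allocation. Under Criteria for discontinuation, a therapist's judgement can lead to withdrawal from the trial, and only one arm has a trial therapist. Those who ask to leave the trial are then contacted only for an exit survey. The documents do not show that such a difference will occur or how large it would be.

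At stake is a published between-group CI that readers may use when thinking about the definitive trial. This is not a detail left to a later analysis plan, because the article positively rules out any alternative, even as a sensitivity analysis.

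**Working it through.** **Inputs from the Protocol article.** 48 participants, 24 per arm; 17% expected attrition; retention criterion 60%; candidate outcomes at baseline, 3, 6 and 9 months.

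**The plan's own figure.** The stated precision of the attrition estimate is ±15 points. 1.96 × √(0.17 × 0.83 / n) gives 0.150 at n = 24 and 0.106 at n = 48. The figure is therefore reproduced for one arm and is conservative for the whole sample.

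**Retention criterion.** 0.60 × 48 = 28.8, so 29 of 48 (60.4%) is needed. That total is reached by 24/24 and 5/24 (100% and 21%), by 20/24 and 9/24 (83% and 38%), or by 17/24 and 12/24 (71% and 50%). The pooled figure cannot tell these apart.

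**Bias of the complete-case difference.** Assumptions, none of which come from the documents:
- SD 1 and equal correlation between visits of 0.5 or 0.7
- true effect 0 or −0.5 SD
- where loss is score-related, the log-odds of drop-out change by 1 per SD of the 6-month score
- 3- and 6-month scores observed for everyone, with loss occurring only at month 9
- 200,000 simulated participants per arm; site and medication status not modelled

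| Loss by 9 months | Relation of loss to the 6-month score | Absolute bias (SD) |
|---|---|---|
| 17% in each arm | none | about 0 |
| 17% or 40% in each arm | same in both arms | within 0.01 |
| 17% in each arm | one arm only | 0.08 to 0.11 |
| 25% v 9% (17% overall) | same in both arms | 0.07 to 0.09 |
| 17% in each arm | opposite directions | 0.15 to 0.21 |
| 40% in each arm | one arm only | 0.16 to 0.24 |
| 40% in each arm | opposite directions | 0.33 to 0.47 |
| 60% v 20% (40% overall) | same in both arms, or one arm only | 0.16 to 0.35 |

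Predicting the missing 9-month score within arm from baseline, 3 and 6 months left at most 0.006 SD of bias in every row. Adjusting completers for baseline alone left 0.03 to 0.04 SD in the 17%, one-arm row. The complete-case SD fell by at most about 4%.

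**Scale.** The 95% CI half-width in SD units is 1.96 × √(1/n₁ + 1/n₂):
- 20 per arm (17% loss): 1.96 × √(2/20) = 0.62
- 14.5 per arm (about 40% loss): 1.96 × √(2/14.5) = 0.73
- 60% v 20% loss (9.6 and 19.2 retained): 1.96 × √(1/9.6 + 1/19.2) = 0.77

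**At the trial's actual size.** 1,500 simulated trials of 48 used an adverse setting: true effect −0.30 SD, correlations 0.5 to 0.65, random 17% loss under usual care, and score-related loss averaging 22% in the intervention arm. The mean estimate (SD of the estimate) was −0.452 (0.326) for complete case, −0.394 (0.290) for complete case with baseline, and −0.313 (0.284) for likelihood-based repeated measures. In a large-sample check at 22% loss and correlation 0.65, a bias of 0.15 SD needs a log-odds slope of about 1.4, a roughly four-fold rise in the odds of drop-out per SD.

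**The case against.** The strongest case against is that this is a feasibility trial. Its primary outcomes are recruitment, attrition and acceptability. The 9-month difference has no p value and enters none of the four continuation criteria. At the planned attrition the likely bias is well inside the CI. Losses at each visit are to be reported with CIs, and leavers are asked their reasons. All of this stands and limits the weight of the point. It does not explain why scores already collected should be barred from the analysis.

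Several stronger readings are tempting, and the documents do not support them:
- *Any outcome-related drop-out biases the difference.* It does not. The same relation at the same rate in both arms gave a bias near zero, even at 40% loss.
- *The intention-to-treat statement is contradicted.* The article uses the term for analysis by allocation and openly states the complete-case restriction. The fair criticism is only that randomised people without a 9-month score drop out of the estimate.
- *The SDs for the future sample size are seriously distorted.* The shrinkage was about 4% at most.
- *The interim scores bring a large gain in precision.* In the trial-size simulation the SE fell 13% from unadjusted complete case (0.326 to 0.284), but baseline adjustment alone reached 0.290. The 3- and 6-month scores added about 2%.
- *The 60% criterion is faulty because it misses differential loss.* It is a feasibility threshold, not a bias check. The 24/24 versus 5/24 split shows what it permits, not what is likely. Turning it into a pass/fail rule for each arm is debatable and is not needed here.

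**Conclusion.** The point holds in a limited form. The plan forbids any use of the baseline, 3- and 6-month scores of people lost by 9 months, and this leaves the reported difference open to bias if drop-out differs by arm. The size is about 0.1 SD at 17% attrition, up to about 0.2 SD if the arms lose people in opposite directions. Near the 60% limit with unequal loss it is 0.16 to 0.35 SD. The CI half-widths are 0.62 SD at 17% attrition and 0.73 to 0.77 SD near the limit.

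These figures rest on the assumed correlations and drop-out relation. They also assume that the 3- and 6-month scores are available, so for people lost before those visits the interim data would recover less. The change is worth making because it is cheap and needs no new data, but nothing in the feasibility decision depends on it.

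**What to change.** In Quantitative data analysis, and in the analysis plan, delete the prohibition on handling missing data and restrict the complete-case rule to a supporting analysis. Then:

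1. For continuous outcomes measured at every visit, estimate the 9-month difference with a likelihood-based repeated-measures model on the 3-, 6- and 9-month scores. Include baseline score, arm-by-visit terms, site and medication status. Report the 95% CI without a p value, as now, with the complete-case result beside it.
2. For the observer-rated scales, which have no 3- or 6-month values, add the baseline score as a covariate. In the simulations this removed half or more of the bias, but not all of it.
3. Report 9-month retention by arm next to the pooled 60% criterion. The criterion itself can stay as it is.

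The cost is a change of wording and slightly more analysis, settled before outcomes are examined by arm. The model assumes data missing at random given the observed scores, which cannot be tested. Showing the complete-case result alongside lets readers see how much the handling of missing data matters.

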### Sample size

A total of 48 participants (24 per group) will allow us to address the stated objectives of this feasibility trial. This represents recruitment to three ThrIVe-B groups at full capacity (8 per group), with equivalent numbers randomised to TAU. On the basis of our previous work on the ThrIVe-B programme, we estimate an attrition rate of 17% with respect to the primary end point at 9 months post-randomisation. Our sample size of 48 will allow us to estimate this level of attrition for a future definitive trial with a precision of ±15% with 95% certainty and allow us to estimate the SDs for any potential primary outcome measures that would inform the power calculation for a definitive trial.

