### Randomisation, concealment of allocation, and blinding

Eligible participants will be randomised in a 1:1 ratio, with minimisation by trial site and medication status. To ensure concealment, eligible participants will be randomised via a validated password website hosted by the Exeter Clinical Trials Unit. The first ten participants will be allocated using simple randomisation, the remainder being allocated using the minimisation procedure, maintaining a stochastic element to the algorithm to allow concealment to be maintained. Following randomisation of a given participant, he or she will be informed of their allocation by an unblinded member of the research team.

Researchers conducting follow-up assessments will be blind to study arm allocation and will remind participants of the need to conceal their allocation. We will test blindness by asking researchers to indicate at follow-up which treatment they believe the participants received and analyse any correlation with outcome. We will maintain the blinding as far as possible to maintain the quality and legitimacy of the trial and its findings; however, in the unlikely event that a participant has an adverse reaction to either treatment arm, unblinding may occur. We will unblind the researchers only in exceptional circumstances when the knowledge of the treatment arm is deemed essential to the management of the patient by their GP (e.g., serious adverse events). Any unblinding that occurs will be recorded; where possible, researchers who remain blind to participant status will conduct their future follow-up assessments. All statistical analyses will be performed by a statistician using groups indicated by an anonymised code.

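### Economic between-group CIs fall under two unreconciled adjustment rules, and the power argument does not justify leaving out the minimisation factors

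*Protocol article*

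**What the plan says.** All of this is in the protocol article. Under Quantitative data analysis, inference is confined to continuous outcomes at 9 months and takes the form of a 95% CI for the mean difference without a p value. The adjustment rule is "Inferential analyses will include the randomisation covariates: site and baseline medication status". These are the factors used for allocation: "Eligible participants will be randomised in a 1:1 ratio, with minimisation by trial site and medication status" (section on randomisation, concealment and blinding).

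A later paragraph of the same section turns to the economic analysis. It states "No covariate analysis or subanalysis will be conducted, because this is a feasibility trial and is not powered for such inferential analyses" and then "Descriptive data for each arm will be reported with CIs for between-group comparisons". It names no time point for those CIs and does not say how it relates to the general rule.

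Under Secondary outcome measures the plan says that "participants will complete the EuroQoL 5-dimension 5-level (EQ-5D-5L) instrument", together with the SF-36 and a resource use questionnaire. Their stated purpose in this trial is to learn whether they can be used in this population.

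**The concern.** There are two difficulties.

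First, EQ-5D-5L and SF-36 scores are continuous and are listed as secondary outcomes, so the general rule reaches them at 9 months. They are also economic measures, so the economic paragraph reaches them too. The first rule adjusts for site and medication status. The second, on its plain wording, does not. Two different CIs for the same difference could each be presented as the planned one. Resource use or cost raises the same question.

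Second, the reason given does not support the decision. A shortage of power argues against looking for effects within subgroups or for interactions. Adjusting a between-arm difference that will be reported anyway is a different matter: it asks no extra question of the data. The plan adjusts its other continuous outcomes in the same 48 participants, so the reason cannot apply to one set of CIs and not the other.

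At stake are the clarity of pre-specification and some precision in the economic estimates.

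**Working it through.** **The plan's own figure.** The only sizing figure is the attrition precision, "with a precision of ±15% with 95% certainty". For a proportion of 0.17 and 48 participants, 1.96 × √(0.17 × 0.83 / 48) = 0.106, or ±10.6 points. With 24 it is 0.150. The printed figure is therefore conservative for the whole sample and matches a single arm. Nothing below depends on it.

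**Inputs from the document.** "A total of 48 participants (24 per group) will allow us to address the stated objectives of this feasibility trial" and "we estimate an attrition rate of 17% with respect to the primary end point at 9 months post-randomisation". Complete cases: 48 × 0.83 = 39.8, taken as 40, or 20 per arm. Analysis is on complete cases only.

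**Inputs that are assumed.** The document gives no correlation between baseline and 9 months for any economic measure, and no share of variance explained by site and medication status. I use ranges. Errors are taken as normal.

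**Step 1: site and medication status only.** This is the only difference between the two stated rules. The simulation had 3,000 runs per setting and 40 participants. The first ten were allocated by simple randomisation and the rest by minimisation on two binary factors with an assumed 0.8 biased coin. A t-based 95% CI was computed with and without the two factors. Monte Carlo error on coverage is about √(0.95 × 0.05 / 3000) = 0.4 points. Half-widths are means in SD units.

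| Variance explained | Coverage, unadjusted | Coverage, adjusted | Half-width, unadjusted | Half-width, adjusted | Adjusted / unadjusted |
|---|---|---|---|---|---|
| 0% | 94.9% | 94.7% | 0.636 | 0.640 | 1.01 |
| 10% | 96.3% | 95.3% | 0.637 | 0.607 | 0.95 |
| 20% | 97.1% | 95.2% | 0.638 | 0.570 | 0.89 |
| 30% | 97.4% | 94.5% | 0.638 | 0.535 | 0.84 |

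Adjusting therefore narrows the interval by about 5%, 11% and 16% in the last three rows. The same comparison with the adjusted interval as the base makes the unadjusted one about 5%, 12% and 19% wider (0.637/0.607, 0.638/0.570, 0.638/0.535).

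**Step 2: adding the baseline value of the same measure.** This goes beyond the plan's general rule.

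- Unadjusted half-width: t(0.975, 38) × √(2/20) = 2.024 × 0.316 = 0.640 SD.
- Adjusted half-width with three covariates: t(0.975, 35) × √((1 − r²) × 2/20) × √(1 + 3/34), where t = 2.030. The last factor is the approximate cost of chance imbalance in the covariates. Site and medication status are assumed to add nothing beyond the baseline value.

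| r | Adjusted half-width (SD) | Change in width |
|---|---|---|
| 0 | 0.670 | +5% |
| 0.3 | 0.639 | 0% |
| 0.5 | 0.580 | −9% |
| 0.7 | 0.478 | −25% |

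The baseline value pays for itself only above a correlation of about 0.3.

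**The case against.** The strongest reply is that nothing conflicts. The economic paragraph stands apart and can be read as a specific exception to a general rule. Alternatively, covariate analysis, paired as it is with subanalysis, may mean exploring covariate effects, for which the power reason is fair. Both readings are possible, so calling the paragraphs contradictory would go too far. But the text does not choose between them, and they lead to different CIs. On the exception reading the stated reason still fails.

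A reader might infer that the plan throws away baseline data it has collected. The document does not establish this. The look-back wording of the resource use questionnaire implies a baseline collection, but no time points are given in the text for EQ-5D-5L or SF-36, and the schedule figure is not available here. The general rule names no baseline score either, so leaving one out is no departure from it.

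The missing time point for the economic CIs is silence. The 9-month limit in the general rule can simply apply.

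A reader might also claim a larger and certain gain. Shrinking the width by √(1 − r²) and correcting only the t quantile gives about 8% to 28% for r from 0.4 to 0.7. That leaves out the cost of chance imbalance, starts above the break-even point, and concerns a covariate that neither rule mentions.

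Finally, the economic measures are here to test feasibility, and the cost-effectiveness ratio is left to the future trial. That stands, and it limits the weight of the point.

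**Conclusion.** The point holds as a minor one. Two rules for the economic between-group CIs are left unreconciled, and the power argument is valid for subgroup analyses but not for adjusting a CI that will be reported.

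The size is modest and rests wholly on assumed inputs with about 40 complete cases. Leaving out the minimisation factors makes the CIs mildly conservative, with coverage of about 96% to 97% if the factors explain 10% to 30% of the variance, and has no material effect if they explain none. The error is towards intervals that are too wide, so the unadjusted CIs would not give false precision. None of the four continuation criteria uses an economic CI, and no p values are reported, so no decision named in the protocol turns on this. It is an improvement that costs nothing, not a defect that threatens the trial's conclusions.

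**What to change.** Restrict the sentence in the economic paragraph to subgroup analyses, where the power reason belongs. Then state that between-group differences in EQ-5D-5L, SF-36 and resource use or cost at 9 months are reported with 95% CIs adjusted for site and baseline medication status, as for the other continuous outcomes. Arm-level summaries stay descriptive and unadjusted.

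As an option beyond the present rule, add the baseline value of the same measure where it was collected. This helps only if the correlation with the 9-month value exceeds about 0.3.

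If unadjusted economic CIs are really intended, say so as an explicit exception and give a reason other than power.

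The cost is two or three sentences of wording and two covariates in models of about 40 participants. Both are known for every participant because the minimisation uses them. No new data are needed.
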